## Abstract

**Background:**

Individuals with schizophrenia or bipolar disorder face a significantly elevated risk of obesity, primarily due to weight gain associated with psychiatric medications and lifestyle factors. While digital self-monitoring tools offer scalable solutions, their application remains underexplored in psychiatric populations. To address these gaps, this type 1 hybrid effectiveness-implementation study investigates the preliminary effectiveness and implementation feasibility of a mobile health-assisted weight management intervention for patients with severe mental illness.

**Objective:**

This study aims to evaluate the preliminary effectiveness and implementation feasibility of a mobile health–assisted weight management intervention for patients with severe mental illness transitioning from inpatient care to community-based recovery.

**Methods:**

This single-center, open-cohort stepped-wedge cluster randomized trial with a 2-month step duration will recruit 204 patients from 6 clinical units. Clusters are randomized into 2 waves, with staggered transitions to a digital intervention, including smart scales, health apps, and biweekly educational modules, over a 6-month observation period. The design evaluates the intervention across the transition from inpatient care to community-based recovery. The primary outcome is the proportion of participants achieving ≥5% weight loss at month 6. Implementation feasibility is assessed through device technical success and intervention adherence (defined as ≥50% completion of weekly weigh-ins and daily dietary logs).

**Results:**

Participant data collection began in May 2023 and was completed by June 2025 with a total of 204 participants. The publication of key findings and results is anticipated in late 2026.

**Conclusions:**

This protocol describes a pragmatic, technology-supported intervention designed to address metabolic side effects in a tertiary psychiatric setting. By bridging the gap between acute hospitalization and community recovery, this hybrid stepped-wedge cluster randomized trial provides a crucial framework for integrating digital metabolic monitoring into routine clinical workflows for vulnerable populations.

## Introduction

### Background

Patients with severe mental illness (SMI) face a 2‐3-fold higher prevalence of obesity and metabolic syndrome than the general population, contributing to 15‐20 years reduced life expectancy [1-3]. These comorbidities lead to elevated cardiovascular risk, impaired treatment adherence, and diminished social functioning [2,4-6]. This metabolic burden is driven by a complex interplay of factors, primarily the metabolic side effects of antipsychotic medications, compounded by sedentary lifestyles and poor dietary habits [7-9].

Although China is undergoing rapid mental health reform, metabolic monitoring in patients with SMI remains insufficient. Available data suggest that the prevalence of comorbid obesity among patients with schizophrenia in China is approximately 16.4% [10]; however, systematic metabolic screening is rarely implemented in routine psychiatric care. Globally, treatment guidelines have long recommended regular physical health monitoring for patients with SMI; only 38% of them receive guideline-concordant metabolic screening [11,12]. The National Institute for Health and Care Excellence has issued updated clinical guidelines advocating mandatory annual BMI surveillance as a preventive measure for individuals with chronic health conditions [13]. This recommendation aligns with emerging epidemiological evidence demonstrating that systematic BMI monitoring reduces obesity-related complications by 22% (95% CI 15%‐28%) in populations with long-term multimorbidity [14].

Digital health technologies have emerged as a particularly promising avenue for delivering these interventions. Recent meta-analyses indicate that comprehensive digital programs incorporating nutritional tracking, exercise prescription, and peer support can achieve a clinically meaningful mean weight reduction of 3.2 (95% CI 2.1‐4.3) kg over 3 months in SMI populations, with notably higher retention rates than traditional in-person interventions [15]. Mobile health (mHealth) tools, in particular, have demonstrated superior adherence and weight loss outcomes compared to paper-based methods [16], and comparable outcomes compared to in-person programs [17,18]. However, significant limitations and gaps in the current evidence base remain, which are particularly relevant when considering the generalizability of findings to Chinese psychiatric settings. Many existing studies are characterized by small sample sizes that preclude examination of clinical heterogeneity and the identification of patient-level predictors of success [19,20]. Furthermore, there is an overreliance on step-counting wearables that neglect other critical metrics like body composition and dietary intake [19]. Crucially, the follow-up durations in most trials are insufficient to assess the long-term sustainability of weight loss and behavioral changes [18,20].

The evidence specific to Chinese SMI populations is even scarcer. While digital health is rapidly expanding in China, most mHealth studies for chronic disease management have excluded or underrepresented individuals with SMI, overlooking the unique cognitive, motivational, and socioeconomic barriers this group faces [21,22]. The bidirectional mental health impacts of digital weight management also remain unclear and potentially complex. While some studies report ancillary benefits such as reduced depressive symptoms following mHealth interventions (β=.31, *P*=.02) [23], others warn of potential harms, including exacerbated body image concerns or anxiety related to constant self-monitoring [20]. These mixed findings underscore the need for careful implementation and evaluation.

To address these challenges, we designed an mHealth-assisted intervention specifically targeting antipsychotic-induced obesity in a Chinese SMI population and evaluated it using a stepped-wedge cluster randomized trial (SW-CRT) to balance rigor with pragmatic implementation.

The SWIM intervention is grounded in social cognitive theory (SCT) and self-regulation principles, which suggest that behavior change arises from dynamic interactions between personal, behavioral, and environmental factors [21,22,24]. Specifically, the intervention targets core SCT constructs, self-monitoring, self-efficacy, and observational learning, using digital tools like food diaries and biometric tracking to provide necessary feedback for behavioral adjustment [25,26]. Clinical adaptations address the specific cognitive and behavioral barriers faced by individuals with schizophrenia and bipolar disorder [27]. The theoretical pathway from digital inputs to clinical impact is illustrated in Figure 1. The framework delineates the pathway from technical inputs (smart scales and mobile apps) to clinical impact. Specifically, it highlights how core activities, such as educational sessions and biometric tracking, generate measurable outputs, including weigh-in frequency, dietary logging completion, and app engagement, which serve as the behavioral foundation for improving health knowledge and fostering self-efficacy. These intermediate changes are hypothesized to drive the primary outcome of weight loss and the long-term impact on overall health. To examine the mechanism of action, this trial will measure self-monitoring frequency and self-efficacy as key process variables. We hypothesize that improvements in these constructs will mediate the intervention’s effect on weight loss.

The model illustrates the progression from digital inputs and activities to measurable implementation outputs (engagement) and clinical outcomes, mediated by SCT constructs.

This trial uses a type 1 hybrid implementation-effectiveness design to concurrently evaluate clinical outcomes and implementation feasibility within a stepped-wedge framework.

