## Methods

### Study Design

This study uses a pragmatic, open-cohort SW-CRT with a 2-month step duration. The trial spans a total observation window of 6 months across 6 clinical units at a tertiary hospital in Beijing. The SW-CRT design ensures that all participants eventually receive the intervention, fulfilling ethical requirements for this high-risk population, while the staggered rollout allows the implementation team to maintain high fidelity by providing intensive technical training for 1 wave at a time.

The trial addresses the dynamic turnover of psychiatric hospitalizations (average stay 4‐6 wk) by defining each cluster as a clinical unit rather than a fixed physical location. The research team comprises trained research assistants, certified nutritionists, and sports physicians. Participants are typically enrolled during their stable recovery phase in the ward; however, the intervention is designed to be portable. Following discharge, the intervention continues remotely, with the same clinical team providing longitudinal oversight via digital clinician dashboards. This approach enables the evaluation of the intervention across the transition from inpatient care to community-based recovery.

The 6 units were randomized into 2 waves (3 units per wave) using a matched-pair constrained randomization approach. To ensure baseline balance, units were paired based on clinical setting and demographics. Allocation was managed by an independent biostatistician via REDCap (Research Electronic Data Capture; Vanderbilt University) and remained concealed from the recruitment staff and participants.

The study timeline is structured into three distinct phases:

Baseline phase (month 1): all clusters receive usual care to establish stable baseline metrics.Transition phase (2 weeks): a staggered 2-week period for device distribution and technical training, occurring at month 1 for wave 1 and month 3 for wave 2.Intervention phase: active digital monitoring lasting 5 months for wave 1 (months 2-6) and 3 months for wave 2 (months 4-6).

This open-cohort approach accounts for the dynamic turnover of psychiatric hospitalizations, allowing for individual enrollment while maintaining randomization at the cluster level (Figure 2).

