### Intervention Program

The SWIM intervention is a multicomponent digital health program grounded in SCT, designed to enhance self-regulation for weight management. Participants are provided with a Huawei Pro 3 Bluetooth-enabled smart scale and the Huawei Health App (v10.0.2) installed on their personal smartphones. The intervention is coordinated by a multidisciplinary research team, including a trained research assistant for technical setup, a certified nutritionist for dietary content, and a psychiatrist for clinical oversight.

The program follows a hybrid delivery model, initiating in the psychiatric inpatient units of Beijing Anding Hospital and continuing remotely in the participants’ community settings post discharge. During the 2-week transition period, participants receive in-person training on biometric tracking and dietary logging. The intervention lasts for the duration of the assigned wave (5 months for wave 1 and 3 months for wave 2). Participants are instructed to perform weekly weigh-ins and daily dietary logging. To support behavioral change, biweekly educational modules are delivered via WeChat (Tencent) groups. See Multimedia Appendix 1 for the smart scale setup guide and weighing protocol. Furthermore, weekly automated push notifications and personalized feedback messages are sent via messages, with content tailored to each participant’s specific weight trajectory (Table 1).

**Table 1. T1:** Summary of SWIM intervention components.

Components	Delivery method	Frequency
Smart scale weigh-ins	Digital Health App and compatible smart scale	Weekly (at least once per week)
Dietary logging	Digital Health App	Daily (all meals and snacks)
Education session	WeChat groups	Biweekly
Behavior enhancing	Message prompts and tips	Weekly (Automated push notifications and personalized feedback)

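### Self-monitoring frequency is recorded only under the intervention, so the hypothesis that it mediates weight loss reduces to an adherence-response association within intervention periods

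*Protocol article*

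**What the plan says.** The theoretical framework in the Background section names two process variables: "this trial will measure self-monitoring frequency and self-efficacy as key process variables". It continues: "We hypothesize that improvements in these constructs will mediate" the effect on weight loss. The same section describes self-monitoring through the programme's own activities, which "generate measurable outputs, including weigh-in frequency, dietary logging completion, and app engagement".

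The other sections show when such data can arise:

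- **Intervention Program:** "Participants are provided with a Huawei Pro 3 Bluetooth-enabled smart scale", together with the health app. Table 1 of the article delivers weigh-ins through the scale and app, and dietary logging through the app.
- **Study Design:** in the baseline month "all clusters receive usual care to establish stable baseline metrics". Devices arrive in the transition phase, "a staggered 2-week period for device distribution and technical training, occurring at month 1 for wave 1 and month 3 for wave 2".
- **Secondary Outcomes:** good adherence is scored from the share of expected weekly weigh-ins and from dietary logging over the intervention period. The named scales include a visual analogue scale for the intent to lose weight, but none for self-efficacy.
- **Secondary Objectives:** a separate hypothesis expects better adherence to go with better clinical and metabolic results.

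**The concern.** A mediation claim compares the mediator with and without the intervention, and then relates the mediator to the outcome. Here the first comparison carries no information. Without a scale and app, device-based weigh-in and logging frequency is either unrecorded or zero, so it rises at crossover whatever the participant does.

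The second relation can then be learned only from people already receiving the intervention, where it is an ordinary association between adherence and outcome. Several features of the programme make that association hard to read causally:

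- Feedback messages are tailored to each participant's weight course, so weight can drive engagement.
- Low engagement triggers reminders, counsellor outreach and then in-person support (Outcomes and Measures, Overview), so low self-monitoring changes the support received.
- Motivation may raise both logging and weight loss.

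At stake is what the trial may conclude about mechanism. The estimate of the overall intervention effect is not affected.

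**Working it through.** The plan gives no figure for mediation, so there is none to reproduce. Two checks apply.

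**1. Where the mediator can be observed.** The inputs are from Study Design: 6 units, 2 waves of 3 units, a 6-month window, and intervention in months 2-6 (wave 1) and months 4-6 (wave 2).

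- Total cluster-months: 6 × 6 = 36.
- Control, wave 1: 3 × 1 = 3.
- Control, wave 2: 3 × 3 = 9.
- Control in all: 3 + 9 = 12. Intervention: 36 − 12 = 24.
- Both conditions run side by side only in months 2 and 3.

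These counts are before the 2-week transitions are removed. On the data collection described, device-based self-monitoring is absent or zero by construction in all 12 control cluster-months. Cluster-months are the right unit: in an open cohort with continuous recruitment, individuals need not contribute every control month of their unit.

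**2. What a fitted model would deliver.** This is an illustrative simulation at individual level without clustering, with 2000 runs and 102 participants per condition (half of 204). All settings are assumptions except the total effect of 0.40 SD, which matches the target effect size in Sample Size Estimation.

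- Mediator M: fixed at 0 in control; under the intervention, mean 0.5 and SD about 0.2 (a proportion of expected self-monitoring).
- Outcome Y: weight loss in SD units. The model is Y ~ A + M, where A is the intervention.
- Indirect effect: mean of M under the intervention × fitted slope of Y on M.

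| Scenario | True indirect | True direct | Mean estimated indirect (SD over runs) | Mean estimated direct |
|---|---|---|---|---|
| Full mediation, no confounding | 0.8 × 0.5 = 0.40 | 0 | 0.40 (0.26) | −0.01 |
| No mediation, no confounding | 0 | 0.40 | 0.00 (0.25) | 0.40 |
| No mediation, motivation drives both M and Y (coefficient 0.3 on Y) | 0 | 0.40 | 0.54 (0.26) | −0.14 |

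The third row can be checked by hand. Motivation enters M with weight 0.2 × 0.7 = 0.14, and the variance of M is 0.2² × (0.7² + 0.71²) = 0.0398. The spurious slope is 0.3 × 0.14 / 0.0398 = 1.06, and 1.06 × 0.5 = 0.53, close to the simulated 0.54. The direct effect absorbs the difference: 0.40 − 0.54 = −0.14.

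The variance of M in control is zero in every scenario. The slope therefore comes entirely from intervention periods, and the model's assumption that the slope is the same in both conditions cannot be examined.

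**The case against.** The strongest reply is that the analysis is not impossible. Self-monitoring varies among treated participants, which is why the plan sets an adherence cut-off and an outreach ladder. A mediator fixed at zero in control still leaves a slope to estimate, and the first two simulated scenarios recover the truth when there is no confounding. This stands. A reader might infer that the mediator is the same thing as treatment, or that the indirect effect is unidentified at any sample size; the documents support neither.

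A reader might also infer that the stepped wedge prevents the test. It does not. Visits at months 0, 1, 2, 3 and 6 fall in both conditions, and self-weighing could have been asked about in control periods. The limit lies in the measurement plan. That recording starts only with device issue is itself a well-supported inference, not an explicit statement. The paper log in Ethical Considerations and Data Security is a backup for technical failure, not a usual-care measure.

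Confounding and reverse causation threaten any mediation analysis, since mediators are not randomised. This is true, and a control-phase measure would not remove them. Without one, however, nothing remains beyond the adherence association.

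The hypothesis also covers self-efficacy, which a questionnaire could capture in both conditions, so late device issue does not defeat that half. The article names no such scale, but the assessment schedule in Multimedia Appendix 2 is not shown. It cannot be concluded that self-efficacy went unmeasured.

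Finally, mediation is not among the primary, secondary or exploratory objectives, and a condensed article may leave the model to the analysis plan. The absence of a model is therefore no fault. The point concerns the stated hypothesis and the measurement described for it.

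**Conclusion.** The point holds for self-monitoring frequency, as a limit on interpretation. The variable is an output of the intervention, no value is described for the 12 of 36 control cluster-months, improvement in it has no comparator, and the intervention-to-mediator path holds by construction. An indirect effect can be estimated only by assuming no mediator-outcome confounding and no intervention-by-mediator interaction. The first is implausible given tailored feedback and outreach triggered by nonadherence; the second cannot be checked. The result would be an adherence-response association within intervention periods, not evidence of mechanism.

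The verdict takes the six-month schedule at face value and assumes that no usual-care measure was collected without being described. The 0.54 SD shows a direction and a possible order of size under assumed values; it does not predict this trial's bias. Severity is low: the sentence stands in the Background section and the main effectiveness analyses are untouched.

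**What to change.** In the Background section, restate the self-monitoring hypothesis as an adherence-response association within intervention periods, in line with the hypothesis already in Secondary Objectives. Specify it in time order, with weigh-in and logging frequency in one interval predicting weight change in the next. State that residual confounding remains, because the lag orders events in time but does not remove shared causes.

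Keep self-efficacy as a mediator only if a scale was completed in both control and intervention periods, and name that scale; otherwise drop it.

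The Results section reports follow-up as finished and analysis in progress, so a control-phase measure can no longer be added. If one was collected but not described, describe it. The cost is a change of wording and one lagged analysis. The downside is a weaker claim about mechanism.

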**Figure 1. F1:**
[figure not shown]
Theoretical framework and logic model of the intervention.

### Primary Objective

The primary objective is to evaluate the effectiveness of the digital intervention on body weight reduction. The primary outcome is the proportion of participants achieving ≥5% weight loss at the end of the intervention phase compared to the control phase. This threshold, along with the ≥7% threshold, is selected based on established evidence linking these levels of weight loss to significant cardiovascular and metabolic health benefits in the SMI population [28-31]. Based on recent trials of tailored digital interventions in similar populations, which reported ≥5% success rates ranging from 15% to 36.6% [32], we anticipate that the intervention will achieve a success rate of at least 40%, significantly higher than the expected 20% success rate in the control phase.

### Secondary Objectives

Secondary objectives focus on capturing granular metabolic improvements and assessing implementation feasibility. To fully evaluate metabolic change beyond binary thresholds, we will analyze absolute changes in body weight (kg) and BMI as continuous outcomes. Additional clinical assessments include changes in fasting blood glucose, lipid profiles, and self-reported psychosocial functioning. Feasibility is evaluated through device technical success (smart scale pairing rates), participant adherence (frequency of weekly weigh-ins and dietary logs), and digital usability scores. We hypothesize that the intervention will demonstrate good feasibility, defined as ≥50% adherence to weekly weigh-ins, and that higher adherence will correlate with greater improvements in clinical and metabolic outcomes.

### Exploratory Objectives

As a hypothesis-generating component, we will explore individual-level predictors of clinical success and engagement, including digital literacy, baseline psychopathology, and medication adherence. These exploratory analyses will be adjusted for multiple comparisons to minimize the risk of type I error.

## Methods

### Study Design

This study uses a pragmatic, open-cohort SW-CRT with a 2-month step duration. The trial spans a total observation window of 6 months across 6 clinical units at a tertiary hospital in Beijing. The SW-CRT design ensures that all participants eventually receive the intervention, fulfilling ethical requirements for this high-risk population, while the staggered rollout allows the implementation team to maintain high fidelity by providing intensive technical training for 1 wave at a time.

The trial addresses the dynamic turnover of psychiatric hospitalizations (average stay 4‐6 wk) by defining each cluster as a clinical unit rather than a fixed physical location. The research team comprises trained research assistants, certified nutritionists, and sports physicians. Participants are typically enrolled during their stable recovery phase in the ward; however, the intervention is designed to be portable. Following discharge, the intervention continues remotely, with the same clinical team providing longitudinal oversight via digital clinician dashboards. This approach enables the evaluation of the intervention across the transition from inpatient care to community-based recovery.

The 6 units were randomized into 2 waves (3 units per wave) using a matched-pair constrained randomization approach. To ensure baseline balance, units were paired based on clinical setting and demographics. Allocation was managed by an independent biostatistician via REDCap (Research Electronic Data Capture; Vanderbilt University) and remained concealed from the recruitment staff and participants.

The study timeline is structured into three distinct phases:

Baseline phase (month 1): all clusters receive usual care to establish stable baseline metrics.Transition phase (2 weeks): a staggered 2-week period for device distribution and technical training, occurring at month 1 for wave 1 and month 3 for wave 2.Intervention phase: active digital monitoring lasting 5 months for wave 1 (months 2-6) and 3 months for wave 2 (months 4-6).

This open-cohort approach accounts for the dynamic turnover of psychiatric hospitalizations, allowing for individual enrollment while maintaining randomization at the cluster level (Figure 2).

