**Figure 2. F2:**
[figure not shown]
Stepped-wedge design matrix across six clinical clusters over 6 months. The figure illustrates the staggered transition from usual care (gray) to the digital intervention phase (blue) following a 2-week transition period (light blue).

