### Informed Consent and Capacity Assessment

Due to the dynamic turnover of psychiatric hospitalizations (average stay 4‐6 wk), we use a consecutive, open-cohort recruitment model. Treating psychiatrists identify potential participants during routine clinical encounters. To prevent anticipation bias, crossover dates are disclosed to each unit’s implementation team only 2 weeks prior to their scheduled transition. This separation of roles ensures that the recruitment process remains objective and independent of the unit’s study phase. Given the vulnerability of the SMI population, a structured capacity assessment is conducted prior to enrollment. Participants must demonstrate comprehension of the study’s procedures, data workflows, and the right to withdraw. Written informed consent is obtained from all participants, with primary family caregivers strongly encouraged to witness the process and co-sign the form to provide an additional layer of advocacy. Signed documents are encrypted and stored securely at the research center.

To systematically assess the representativeness of the study sample, a comprehensive screening log is maintained for all identified patients. We record de-identified demographic and clinical data (age, sex, primary diagnosis, and EHR-derived BMI) for all screened candidates, including those excluded due to lack of smartphone access, weight limits (>150 kg), or refusal to participate. At the trial’s conclusion, a comparative analysis between enrolled participants and the broader hospital population will be performed to quantify recruitment bias and characterize the digital divide within the SMI population.

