#### Clinical Effectiveness Analysis

To account for the nested cluster structure and secular time trends inherent in the stepped-wedge design, we use 2 complementary modeling approaches. For the primary binary outcome (≥5% weight loss), a generalized estimating equations model with a logit link function will be used to compare proportions across study phases. For continuous secondary outcomes (eg, mean percentage weight change and BMI reduction), we will use a Linear Mixed-Effects Model. The model is specified as follows:

Yijk=β0+β1⋅Interventionjk+Σγk⋅Timek+Σδm⋅Covariatesijk+αj+ζij+ϵijk

Where:

Yijk represents the continuous outcome for individual i in cluster j at time k.β1estimates the treatment effect (Intervention vs Control); γk represents categorical secular time trends to isolate the intervention’s impact from time-related fluctuations; and δm denotes fixed-effect adjustments for the prespecified covariates. αj is the random intercept for the cluster (clinical unit) to account for ICC; ζij is the random intercept for the individual to account for repeated measurements over time; and ϵijk represents the residual error.

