## Results

The study has progressed as follows: funding was secured in March 2022, the Ethics Approval was guaranteed in August 2022, and participant data collection began in May 2023 and was completed by June 2025, with a total of 204 participants. The follow-up period was finished in January 2026. Initial data analysis is in progress, and the publication of key findings and results is anticipated by late June 2026. The final trial results will be reported in accordance with the CONSORT extension for SW-CRTs.

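### A 6-month stepped wedge with dated unit crossovers cannot be one calendar rollout spanning May 2023 to January 2026, so the model's time term has no consistent origin and control of secular trends is not shown

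*Protocol article*

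**What the plan says.** The protocol article describes the time axis in two ways.

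**A 6-month cluster-level wedge.** Study Design calls the trial a "pragmatic, open-cohort SW-CRT with a 2-month step duration" and adds that "The trial spans a total observation window of 6 months across 6 clinical units". After a shared baseline month, the schedule is "active digital monitoring lasting 5 months for wave 1 (months 2-6) and 3 months for wave 2 (months 4-6"). The caption of Figure 2 reads "Stepped-wedge design matrix across six clinical clusters over 6 months". The Primary Outcome section places the endpoint at the close of a 6-month study period. Informed Consent and Capacity Assessment says that units learn their crossover dates "only 2 weeks prior to their scheduled transition", which implies a date fixed for each unit.

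**A conduct period of well over two years.** Results says "participant data collection began in May 2023 and was completed by June 2025, with a total of 204 participants", and then "The follow-up period was finished in January 2026". The overview under Outcomes and Measures counts visits from a baseline at month 0, through months 1, 2, 3 and 6.

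**The model.** Clinical Effectiveness Analysis prints one set of time effects, which "represents categorical secular time trends". Treatment is indexed by cluster and time. The other named adjustments are exposure duration since crossover and antipsychotic risk group. Anticipated Findings then claims robust control of temporal confounders through time-trend adjustment.

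**The concern.** In a stepped wedge, treated observations fall later than control observations by design. The comparison is protected only if the time term tracks the clock on which units crossed over, and if both conditions are observed over the period being adjusted for. Here a 6-month matrix is set against 26 months of data collection and 33 months to the end of follow-up, with no statement of how one maps to the other.

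Two mappings are possible, and each leaves part of the text unsupported:

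- **Calendar clock.** Units crossed once, on dates. Most patients would then have joined a unit already on the intervention, and the control comparison would rest on a small early group.
- **Patient clock.** Months run from each person's enrolment. The time term is then time since enrolment, not a secular term, and shifts in prescribing, season or case mix over more than two years have no term in the model.

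A reader of the results could not tell what the treatment effect is compared against, or what it is adjusted for.

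**Working it through.** **1. The schedule against itself.** Months 2 to 6 are 5 months and months 4 to 6 are 3, as stated. Wave 1 has 1 control month (1 + 5 = 6) and wave 2 has 3 (3 + 3 = 6). The design closes exactly on 6 months.

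**2. The schedule against the dates in Results.**

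- May 2023 to June 2025, inclusive: 8 + 12 + 6 = 26 months (25 by difference).
- May 2023 to January 2026, inclusive: 8 + 12 + 12 + 1 = 33 months.
- June 2025 to January 2026: 7 months. This fits enrolment to mid-2025 plus 6 months of follow-up each. The article says data collection, not enrolment, so 26 months of accrual is an inference, though a likely one.

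**3. Patients outside a 6-month calendar window.** Assuming uniform accrual, 204 × 6/26 = 47 (23%) enrol in the first 6 months, or 204 × 6/25 = 49 (24%). The other 155 to 157 (76-77%) enrol later.

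**4. Control data on a calendar clock.** Assume uniform accrual, 102 patients per wave and a rollout starting in May 2023.

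- Enrolled before crossover at months 1 and 3: 102 × 1/26 + 102 × 3/26 = 3.9 + 11.8 = 15.7 of 204 (7.7%; with 25 months, 8.0%).
- With the 2-week transition counted as control, so crossover at 1.5 and 3.5: 102 × 1.5/26 + 102 × 3.5/26 = 5.9 + 13.7 = 19.6 of 204 (9.6%).

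**5. Bias when the model holds only time since enrolment.** A null simulation used 400 replicates of 204 patients with visits at 0, 1, 2, 3 and 6 months, a between-patient SD of 3 kg, a residual SD of 1 kg, no unit effect, and a random-intercept model with visit effects. The SDs and trends are assumptions. The true effect is zero, so each entry is bias in kg.

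| Calendar trend assumed | Patient clock, waves accrue in parallel | Patient clock, wave 1 earlier than wave 2 | Same, calendar month added | Calendar rollout, uniform accrual |
|---|---|---|---|---|
| Linear, -2 kg over 26 months | 0.01 | 0.03 | 0.00 | -0.04 |
| Seasonal, amplitude 1 kg | 0.00 | -0.10 | -0.01 | -0.51 |
| Step, -2 kg at month 13 | 0.00 | 0.07 | 0.00 | 0.20 |

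In the uneven-accrual linear case, adding calendar month raised the SD of the estimate from 0.132 to 0.139 kg. These figures concern continuous weight, not the binary primary outcome.

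**The case against.** The best defence is that a coherent reading exists. The abstract speaks of a 6-month observation period, and visits are counted from each participant's month 0. Six months per participant, 26 months of accrual and follow-up to January 2026 fit together. On that reading randomization still protects the comparison: if both waves recruit side by side, calendar drift affects them alike, and simulated bias is about zero. The origin of a time index is also a detail that an article may leave to the analysis plan.

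Much of this stands, and it limits what can be said. Four stronger readings are tempting and are not supported:

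- **That secular trends are certainly uncontrolled.** This depends on the clock and on accrual by wave. If the time term spans all 33 calendar months, trends are adjusted for, although the effect then rests mainly on the first months.
- **That the treatment term is wrongly indexed on a patient clock.** Status then depends only on wave and month since enrolment, so cluster and time are the right indices.
- **That only 8% of patients have control data.** That figure needs both a calendar rollout from May 2023 and uniform accrual, and the article states neither.
- **That crossover timing could not be concealed.** This follows only on the patient clock, and it is a separate question from time trends.

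The defence does not remove the contradiction. The article prints the model, calls its time term secular and claims robust control. It also gives units dated crossovers and a 6-month study period, which do not fit the patient-clock reading. These are conflicting statements, not omitted detail.

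**Conclusion.** The concern holds as an unresolved contradiction with consequences for the analysis. A single 6-month calendar rollout cannot be squared with the reported dates, the single time term cannot be both calendar time and time since enrolment, and the claimed control of temporal confounders is not shown.

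The size depends on which clock was used:

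- **Calendar clock:** about 16 to 20 of 204 patients would have any control observation, given uniform accrual. Coding time as month since enrolment gave bias of up to about 0.5 kg under the assumed trends.
- **Patient clock:** bias is about zero if the waves accrue in parallel. It reached about 0.1 kg in the one uneven pattern tried, and nearly vanished once calendar month was added.

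The article does not report accrual by wave, so neither size can be fixed from it.

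**What to change.** 1. State which clock defined crossover and the time index in the model. Give the calendar crossover date of each unit, and reconcile Study Design, Figure 2, Informed Consent and Capacity Assessment, Primary Outcome and Results accordingly.
2. Code intervention status per patient-visit from actual dates. This assumes that visit dates are held, which the article does not say.
3. In both the GEE and the mixed model, include time since enrolment plus a parsimonious calendar-time term: linear, a spline, or a few broad periods. Quarter dummies are a poor choice. Enrolment touches 9 quarters and observation 12, so there are about 204/(6 × 9) = 3.8 enrolled patients per unit-quarter. If the GEE clusters on unit, a sandwich covariance from 6 units has rank at most 6.
4. Fit a unit-by-period random effect only as a sensitivity analysis, and only if it can be estimated.
5. Report enrolment and control person-time by wave and calendar period.
6. If crossover was on the calendar, restrict the effect claim to the window in which both conditions were present.

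The cost is rewording, one or two model terms and a slight loss of precision; in the uneven-accrual linear case even full month dummies raised the SD by about 5% (0.139/0.132 = 1.05). Item 6, if it applies, costs far more: with uniform accrual only about 24 patients (204 × 3/26 = 23.5) would have enrolled by month 3. Results says that analysis is still in progress, so the change can be made before findings are reported.
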